**Acronyms**

ART: Antiretroviral therapy

EGPAF: Elizabeth Glaser Pediatric AIDS Foundation

FAM-CARE: Family-centered care program

IDI: In-depth interview

LTFU: Lost to follow-up

MOH: Ministry of Health

PEPFAR: President’s Emergency Plan for AIDS Relief

PMTCT: Prevention of mother-to-child HIV transmission

SOAR: Supporting Operational AIDS Research

SOP: Standard Operating Procedure

USAID: United States Agency for International Development

WHO: World Health Organization

**Definition of Terms**

A “family unit:

For analysis purposes, a “family unit” is defined as a family in which there is at least one HIV-positive child <15 years enrolled in the study receiving ART and there is >1 family member who is also HIV-positive. In the majority of instances, a family will have only one HIV-positive child on ART, and the family “unit” equals one enrolled child plus >1 HIV-positive family member. However, if a family (in intervention or control sites) has more than one HIV-positive child on ART, all children on ART are enrolled, but for sample size purposes, this will equal one enrolled “family unit”. Data from all enrolled children will be included in the analysis with adjustment potential correlations due to family units.

Family-centered care:

The family-centered care approach is a way of caring for children and their families within health services which ensures that care is planned around the whole family, not just an individual, and in which all family members are recognized as care recipients. The approach recognizes the vital role that families play in ensuring the health and well-being of infants, children, adolescents and family members of all ages.

Viral Suppression:

Viral suppression is defined as HIV RNA level below the level of assay quantification (e.g., undetectable viral load, such as HIV RNA <50 copies/mL when the lower limit of the assay is 50 copies/mL). The proportion of patients with HIV RNA >1,000 copies/mL will also be assessed separately.

1. **SUMMARY OF PROPOSED RESEARCH**

SOAR partner Elizabeth Glaser Pediatric AIDS Foundation (EGPAF) proposes to leverage existing and planned service delivery platforms in Swaziland to evaluate a model of care to improve pediatric retention and ART adherence. In the family-centered care (FAM-CARE) program, after identification of HIV infection in a child, active HIV testing of all family members is conducted and all HIV-positive family members are seen together as a unit and receive their care together. EGPAF-Swaziland is in the process of establishing a FAM-CARE service delivery program in selected health facilities in the Hhohho region of Swaziland, and roll-out of these services will provide a platform for this study. Viral load monitoring is in process of national roll-out in Swaziland. The planned study is an implementation science study to evaluate the implementation of the FAM-CARE program in Swaziland and its effect on viral suppression and retention in children living with HIV.

The proposed study will evaluate the effect of implementing a FAM-CARE program on viral suppression and retention in children through enrollment of a prospective cohort of HIV-positive children and their caregivers at sites implementing the FAM-CARE program and control sites continuing the current standard of care. The study will be conducted in four “clusters” of facilities (2 hospitals and 2 health centers and their filter clinics) in the Hhohho region of Swaziland. Two facility “clusters” (one hospital and one health center, with their filter clinics) will be randomized to initiate the FAM-CARE program with viral load monitoring and two “clusters” (one hospital and one health center, with their filter clinics) will be control standard-of care sites. A prospective cohort of HIV-positive children and their caregivers will be followed in the FAM-CARE program sites and control sites. Each child will be followed for 18 months following enrollment. The primary objective is to evaluate the effect of the FAM-CARE program on the rates of viral suppression and retention in care, comparing rates of viral suppression and retention in children enrolled in FAM-CARE vs control sites. The study will also evaluate factors associated with viral suppression and retention (including family demographic characteristics), and conduct qualitative interviews to assess the acceptability of the FAM-CARE program by caregivers and health care providers in the intervention sites.

Since the study is comparing different program models of providing standard-of-care HIV care and treatment in facilities, there is minimal risk to participants enrolled in the study. By simply reorganizing the way services are provided, without additional costs to the program, we anticipate that the FAM-CARE program should provide more efficient and effective services that promote improved retention in care, ART initiation, adherence, and viral suppression for children and also their adult family members. If the family-centered care program is found to be effective in increasing viral suppression in children on ART, EGPAF will work with the Ministry of Health to roll-out the FAM-CARE program to more facilities in the country. Furthermore, should the program to be effective, feasible and acceptable, the program should be easily transferable to other resource-limited country settings, and contribute to the global UNAIDS/PEPFAR 90-90-90 targets by ensuring viral suppression in children on ART.

1. **BACKGROUND AND RATIONALE**

While there has been good progress in prevention of mother-to-child HIV transmission, efforts to scale up antiretroviral treatment (ART) and achieve the World Health Organization (WHO) “90-90-90” targets (90% diagnosis, 90% infected on ART; 90% on ART with viral suppression) have been less robust for children compared with adults (1,2). These discrepancies reflect substantial gaps in essential services and numerous missed opportunities to engage children in care and provide effective ART.

With the 2016 WHO recommendations for universal treatment for all HIV-positive individuals regardless of clinical or immune status, HIV-positive parents and their children will all require ART (3). HIV infection in sub-Saharan Africa occurs in the context of the family, given the predominantly heterosexual nature of HIV transmission and transmission of HIV during pregnancy, delivery and breastfeeding. The family is the basic unit of care for children, with the health and well-being of children inextricably linked to their parents’/caregivers’ physical, emotional and social health; a major aim of ART is to keep the family unit alive and well, benefitting parents and also improving the well-being of their children (4). However, most ART services engage patients as individuals, with little attention to their family or other social contexts. Provision of ART has generally entailed separate adult and pediatric clinics because different areas of expertise and service organization have been required for care of children and adults and because prior treatment guidelines were dependent on CD4 count or WHO clinical stage for ART eligibility and hence parents and children may have qualified for treatment months or years apart. However, comprehensive pediatric HIV treatment, care and support will likely not be achieved if the child is not placed in context of their family. A new paradigm has emerged, with provision of family-centered care that includes all HIV-positive family members and addresses the comprehensive health needs of all the family members, particularly the mother and child (5). Health care services that engage families may offer advantages in terms of improving retention in care and adherence with ART over the long run (6,7).

However, there is a paucity of data on the role of family-focused care on pediatric and adult treatment outcomes. A 7-year retrospective analysis of data following implementation of an integrated family-focused approach to pediatric HIV care in 10 health facilities and 10 community clinics in Uganda reported a 50-fold increase in family units registered in health care (from 70 to 3653), a 43-fold increase in children actively enrolled in care (from 86 to 3726) and a 23-fold increase in children receiving ART (from 86 to 2015) (8). In a study that examined the association between co-enrollment of HIV-positive family members into care and outcomes of women initiating ART for PMTCT in 12 HIV care and treatment programs in 8 sub-Saharan African countries, the risk of loss to follow-up was significantly greater among HIV-positive women who did not have an HIV-positive family member co-enrolled in care compared to those with a family member enrolled (19% vs 3-8% after 36 months on ART, respectively) (9). These limited data suggest that a family-focused care approach may led to improved retention, ART adherence, and viral suppression for both children and adults engaged in such care. However, implementation of such a program has also been found to have challenges, including issues of disclosure to partners and difficulties in engaging male partners (10-12).

Additionally, achieving the third “90” (90% viral suppression) is particularly challenging in children as most programs do not include pediatric viral load monitoring as part of routine care. The use of 2010/2013 WHO immunologic criteria to define treatment failure results in significant misclassification: in a study in Western Kenya, 6% (2 of 34) of children classified as treatment failure actually had undetectable viral load and 65% (45 of 69) of children thought to have treatment success had detectable viral load, supporting WHO recommendations for routine viral load monitoring (13). The potential use of viral load monitoring as a tool to promote adherence has had some evaluation among adults, but not among children. A meta-analysis of 8 studies in 8 countries found a trend for re-suppression following viral load testing with targeted adherence support for HIV-positive adults found to have detectable viremia (14). Studies are critically needed to determine how to optimally implement and use virologic testing among HIV-positive children (15).

In a recent large cross-sectional survey in Malawi and a 2013 systematic review of viral suppression in HIV-positive adults on ART, viral suppression to RNA <1,000 ranged between 61.8-71.2% (intention-to-treat analysis) (16,17). Data on virologic outcomes for children on ART in sub-Saharan Africa are limited. In a cross-sectional survey of viral suppression (RNA <80 copies/mL) among children on first-line ART for > 6 months in 10 nurse-led clinics in Lesotho, viral suppression was found in only 72.3% of 191 children; no predictors for viral outcome were identified (18). Similarly, in a study of 742 HIV-positive children initiating first-line ART in South Africa between 2008-2011, only 62.3% achieved a viral load <50 copies/mL 6 months after ART initiation (19). Somewhat better data on short-term viral response were reported among a small cohort of 69 HIV-positive children initiating ART in Zambia, with 88.5% having viral suppression (RNA <400 copies/mL) at 6 months, but this decreased to 77.8% by 24 months (20). In a descriptive study using data from a pilot program in 2012-2013 of routine viral load monitoring in 12,063 HIV-positive persons (including 580 children <10 years and 588 adolescents 10-19 years) in Shiselweni, Swaziland, 16% were found to have detectable viral load (>100 copies/mL); children had a 2.6-fold and adolescents a 3.2-fold increased odds of having a detectable viral load (29% of children <10 years and 35% of adolescents 10-19 years had detectable viremia) and were less likely to re-suppress at re-testing after adherence counseling (21). Thus, the available pediatric data suggests viral suppression below the level of assay quantification (RNA <50-400 copies/mL) is observed in 62-78% of children after >6-24 months of ART. In a pooled analysis of data from 5,485 HIV-positive children who initiated ART at 7 South African treatment programs with viral load monitoring, the probability of having a single viral load measurement >1,000 copies/mL was 16.9% at 1 year (95% CI 15.8-18.1) and 32.1% (95% CI 30.2-34.1) at 3 years after starting ART; the frequency of ART failure (two viral load >1,000 copies/mL) was 19.3% by 36 months (22). There are many factors that contribute poor overall virologic response to ART and problems with retention and ART adherence in children, many of which stem from the fact that children are dependent upon adults administration of their medications and attendance at clinic appointments; a family-focused program of care may serve to improve both pediatric retention in care and viral suppression.

EGPAF has been supporting the Kingdom of Swaziland since 2003 to prevent mother-to-child HIV transmission (PMTCT) and to provide HIV and AIDS care and treatment services to HIV-positive children and adults. Currently, EGPAF-Swaziland supports 66 health facilities in Hhohho and Shiselweni regions of Swaziland with PMTCT, HIV testing and counseling, ART and tuberculosis services. Through PEPFAR funding, EGPAF Swaziland is planning to establish family-centered service delivery program (FAM-CARE) in selected health facilities in the Hhohho region to provide more efficient and effective services to promote better ART initiation and retention in care for adults and children. The roll-out of these services will provide a platform on which to introduce and evaluate routine HIV viral load testing and monitoring in children. Two of four health care clinic clusters in the regimen will be randomized to initiate the new FAM-CARE service delivery platform, allowing a comparison of pediatric retention and viral load suppression between FAM-CARE program and control facilities.

1. **RESEARCH GOALS AND OBJECTIVES**

The overall aim of this study is to demonstrate whether a FAM-CARE approach to HIV care will improve rates of viral suppression and retention of HIV-positive children in care.

**Primary objectives:**

1. To evaluate the effect of a FAM-CARE program of HIV care on the proportion of HIV-positive children on ART with viral suppression (defined as HIV RNA copies/mL below the level of assay detection) 18 months after enrollment.

*Hypothesis: Children in the FAM-CARE program will have improved viral suppression (undetectable viral load) 18 months after enrollment compared to children in control facilities.*

1. To evaluate the effect of a FAM-CARE program of HIV care on the proportion of HIV-positive children on ART with HIV RNA >1000 copies/mL 18 months after enrollment into the study.

*Hypothesis: Children in the FAM-CARE program will have lower rates of HIV RNA >1,000 copies/mL 18 months after enrollment compared to control facilities.*

**Secondary objectives:**

1. To evaluate the effect of a FAM-CARE program of HIV care on the proportion of children with viral suppression (undetectable HIV RNA levels) and with HIV RNA >1,000 copies/mL at 6 and 12 months after enrollment into the study.

*Hypothesis: Children in the FAM-CARE program will have improved viral suppression (undetectable RNA) and lower rates of HIV RNA >1000 copies/mL at 6 and 12 months compared to children in control facilities.*

1. Determine the individual and family factors associated with viral suppression and HIV RNA >1,000 copies/mLin children 18 months after enrollment in FAM-CARE and control facilities.
2. To evaluate the effect of a FAM-CARE program of HIV care on loss to follow-up (not seen in clinical care >3 months) and ART initiation in HIV-positive children not on ART at study entry.

*Hypothesis: Children in the FAM-CARE program will have lower rates of loss to follow-up and more children initiated on ART compared to children in control facilities.*

1. Evaluate the acceptability of the FAM-CARE program to caregivers and health care providers.

*Hypothesis: The FAM-CARE program will be acceptable to caregivers and health care providers.*

1. **EXPECTED RESULTS**

The FAM-CARE approach is a way of caring for children and their families within health services which ensures that care is planned around the whole family, not just an individual, and in which all family members are recognized as care recipients. The approach recognizes the vital role that families play in ensuring the health and well-being of infants, children, adolescents, and family members of all ages. It is hypothesized that such a family-centered care program will be successful in enrolling HIV-positive children, their HIV-positive mothers and their partners into continuous follow-up through incentivizing care-seeking within a family and reducing barriers to treatment and retention. Through clinic visits involving all HIV-positive family members, health care provider workload is decreased, as they will not have to see individual members of the family on different days; this also benefits the family by decreasing the amount of times they are required to come to the facility for clinic visits or to pick up ART.

Our study will:

- Assess the effect of the FAM-CARE program on rates of viral suppression and HIV RNA level >1,000 copies/mL in HIV-positive children on ART, and factors associated with these endpoints.
- Evaluate the effect of the FAM-CARE program on missed visits, time out of care, and loss to follow-up of HIV-positive children (pre-ART and on ART), compared to the current standard of care program, and the association of these outcomes with viral suppression.
- Assess the effect of the FAM-CARE program on ART initiation among HIV-positive children not on ART at study entry.
- Assess the feasibility and acceptability of the FAM-CARE program to caregivers and health care providers.

In the Swaziland family-centered care program, no additional staff is required for the program. By simply reorganizing the way services are provided, without additional costs to the program, the program should provide more efficient and effective services that promote improved retention in care, ART initiation, adherence, and the primary endpoint of viral suppression for children and also their adult family members. Should family-centered care prove to be effective, feasible, and acceptable, the program should be easily transferable to other resource-limited country settings, and contribute to the global UNAIDS/PEPFAR 90-90-90 targets by ensuring viral suppression in children on ART.

1. **RESEARCH DESIGN AND METHODS**

**a. Overview of Study Design**

As part of implementation of the pilot FAM-CARE program in Swaziland, health care facility clusters have been randomized to initiate the pilot FAM-CARE program (two health care facility clusters) or continue to provide the current standard of HIV care with separate pediatric and adult HIV clinics (two health care facility clusters). Our study will be an evaluation of this pilot program. Our program evaluation will enroll and follow a prospective cohort of HIV-positive children from selected FAM-CARE sites and control sites to assess the effects of the FAM-CARE program on retention and viral suppression in HIV-positive children on ART. Clinical care for the children is provided through the program and not the study; the study is to evaluate the effect of the program on pediatric viral suppression and retention in care. The FAM-CARE program (described below) is being implemented under the USAID-funded AIDSFree project; no aspects of this care program will be supported through SOAR funding. The SOAR funding is solely being used to support the research evaluation of the program’s effect on pediatric viral suppression and retention.

1. **Study Relationships/Related Project**

***Description of HIV Services and EGPAF Program in Hhohho Region***

Swaziland continues to have the highest HIV prevalence in the world of 26% among individuals aged 15-49 years (23). Nurses have been trained to provide ART, allowing decentralization of ART initiation and monitoring to the local clinic level. HIV clinics are usually held daily (at high volume sites, there may be a specific day for pediatric HIV clinic or HIV antenatal care); in many sites it is the same nurse who provides adult and pediatric care.  At the hospital or health center level, there may be a specific pediatric clinic care provider, and more complex HIV cases are followed at this secondary level.  Thus, each hospital/health center has a group of affiliated/referring clinics. After ART initiation, patients are seen at 2 weeks, and then monthly for 6 months; if stable, after 6 months, adult patients are seen every 2-3 month; thus, at minimum patient visits are at least every 3 months. Pediatric patients are generally seen monthly. While Swaziland is planning to move routine viral load monitoring of patients on ART every 6 months, currently viral load monitoring has been primarily restricted to patients with suspected treatment failure.

The country is divided into four administrative regions (Manzini, Shiselweni, Hhohho and Lubombo) and there is variation in HIV prevalence across the four regions. The study will be conducted in the Hhohho region of Swaziland. The region has a population of 282,734. Approximately 53,091 people in the region are living with HIV, with 32,704 receiving ART. Hhohho has a total of 82 facilities of which 41 are public (government and mission) while the rest are privately owned (24). The health sector service delivery system is loosely organized in a four-tier system comprising of: national referral hospitals, regional hospitals, health centers, and primary health care facilities (public health units-PHUs - and clinics). Of the 41 public facilities, 1 is a referral hospital, 1 is a regional hospital, 2 are health centers and the rest are clinics and PHUs.

For easier support and referrals, the two hospitals and two health centers form 4 clusters of care facilities with their affiliated “filter” clinics in the Hhohho region: Dvokolwako cluster and Emkhuzweni cluster (clinics affiliated with health centers) and Mbabane cluster and Pigg’s Peak cluster (clinics affiliated with hospitals). EGPAF supports 38 of the 41 public facilities in Hhohho. Support from EGPAF covers the HIV testing services, prevention of mother-to-child HIV transmission (PMTCT)/maternal neonatal child health (MNCH), tuberculosis (TB), HIV care and treatment for both adults and children. EGPAF support the facilities with lay staff (HTS counselors, Expert Clients, Cough Monitors, Data Clerks); onsite mentorship; onsite and off-site trainings; quality improvement (QI) projects; cluster meetings; pilots for promising approaches; continuing medical education sessions; data quality audits; site renovations and supply of basic needs; and psychosocial support groups.

Table 1 shows the cluster, affiliated clinics, and the number of children 0-14 years newly initiated on ART during 2015 and currently on ART as of 31 December 2015, which was used as a sampling frame for selection of the study sites, based on patient volume.

**Table 1.** Clusters with Affiliated Clinics & Number of Children Aged 0-14 Years on ART, 12/2015

|  | | **Children 0-14 Years on ART 31 December 2015** | |
| --- | --- | --- | --- |
| **Facility Name** | **Facility Type** | **Initiated on ART in 2015** | **Currently on ART** |
| **Dvokolwako Cluster** | | | |
| Dvokolwako Health Centre | Health Centre | 32 | 203 |
| Balekane Nazarene Clinic | Clinic | 9 | 36 |
| Bhalekane Prison | Clinic | 0 | 0 |
| Ekuphileni Clinic | Clinic | 6 | 6 |
| Nyonyane clinic | Clinic | 2 | 5 |
| *Total* |  | *49* | *250* |
| **Mbabane Cluster** | | | |
| Mbabane Govt | Hospital | 22 | 248 |
| Ezulwini Sat. Clinic | Clinic | 6 | 11 |
| FLAS Mbabane Clinic | Clinic | 1 | 1 |
| Hhukwini Clinic | Clinic | 0 | 7 |
| Lobamba ART Clinic | Clinic | 25 | 88 |
| Mahwalala Red Cross ART Clinic | Clinic | 0 | 29 |
| Motshane ART Clinic | Clinic | 5 | 39 |
| Nkhaba clinic | Clinic | 6 | 12 |
| Salvation Army Clinic | Clinic | 5 | 5 |
| Sidwashini Correctional | Clinic | 0 | 0 |
| Sigangeni ART Clinic | Clinic | 5 | 27 |
| Siphocosini Clinic | Clinic | 7 | 20 |
| St. Mary’s Clinic | Clinic | 2 | 1 |
| *Total* |  | *84* | *488* |
| **Emkhuzweni Cluster** | | | |
| Mkhuzweni HC | Health Centre | 28 | 159 |
| Herefords Clinic | Clinic | 6 | 34 |
| Mangweni | Clinic | 17 | 64 |
| Ndwabangeni Clinic | Clinic | 5 | 32 |
| *Total* |  | *56* | *289* |
| **Pigg's Peak Cluster** | | | |
| Pigg’s Peak Hospital | Hospital | 22 | 318 |
| Bulandzeni Clinic | Clinic | 9 | 40 |
| Bulembu Clinic | Clinic | 1 | 34 |
| Horo | Clinic | 3 | 80 |
| Maguga Clinic | Clinic | 4 | 16 |
| Malandzela Clinic | Clinic | 9 | 21 |
| Mshingishingini Clinic | Clinic | 5 | 12 |
| Ndzingeni Clinic | Clinic | 2 | 17 |
| Ngowane Clinic | Clinic | 1 | 15 |
| Ntfonjeni Clinic | Clinic | 11 | 33 |
| Pigg’s Peak Nazarene Clinic | Clinic | 0 | 1 |
| *Total* |  | *67* | *587* |

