The Hhohho region consists of 4 clinic “clusters”; there was random selection (“coin toss” selection) of “clusters” to initiate FAM-CARE vs to continue standard of care. The FAM-CARE program is being initiated at two “clusters” of clinics that were randomly selected while the other two “clusters” will continue standard of care. The Emkhuzweni and Pigg’s Peak clusters were randomly selected to initiate FAM-CARE, while the Dvokolwako and Mbabane clusters will continue standard of care. For the **prospective** **study evaluation of the FAM-CARE program,** enrollment will take place at selected FAM-CARE and control sites, consisting of the hospital/ health center “parent” of the cluster plus the largest filter clinic for the cluster. Thus, study facilities will include 4 facilities that were randomly assigned to initiate the FAM-CARE program (one hospital plus one filter clinic and one health center and one filter clinic) (FAM-CARE site enrollment) and 4 facilities that were randomly assigned to remain standard of care (one hospital plus one filter clinic and one health center and one filter clinic) (control site enrollment) (see **Table 2** below for facilities/patient numbers). However, we may also expand to include additional filter clinics if necessary.

**Table 2:** Cluster Facilities & Number of Children on ART in Study Facilities

| **Facilities (that have been randomized to FAM-CARE program vs control sites) that will enroll children in the FAM-CARE program evaluation** | | **Children 0-14 Years on ART 31 December 2015** | |
| --- | --- | --- | --- |
| **Facility Name** | **Facility Type** | **Initiated on ART** | **Currently on ART** |
| **Dvokolwako Cluster (Control)** | | | |
| Dvokolwako Health Centre | Health Centre | 32 | 203 |
| Balekane Nazarene Clinic | Clinic | 9 | 36 |
| *Total* |  | *41* | *239* |
| **Mbabane Cluster (Control)** | | | |
| Mbabane Govt | Hospital | 22 | 248 |
| Lobamba ART Clinic | Clinic | 25 | 88 |
| *Total* |  | *47* | *336* |
| **Emkhuzweni Cluster (Intervention)** | | | |
| Mkhuzweni HC | Health Centre | 28 | 159 |
| Mangweni | Clinic | 17 | 64 |
| *Total* |  | *45* | *223* |
| **Pigg's Peak Cluster (Intervention)** | | | |
| Pigg’s Peak Hospital | Hospital | 22 | 318 |
| Horo | Clinic | 3 | 80 |
| *Total* |  | *25* | *398* |

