**Figure 1: Schema of Study Design for the Evaluation of FAM-CARE Program Design:**

**Four clusters of Health Care Facilities/Clinics in Hhohho Region Swaziland**

**Two hospital-based clusters with their filter clinics & two health center-based clusters with their filter clinics**

**Random selection of clusters** **(stratified by whether health center vs hospital cluster) to implement** **family-centered model of care or continue standard care**

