However, there is potential correlation of viral outcomes of children from the same family as well as children from the same facility, thereby violating the assumption of independence required for validity of the chi-square test. We propose to use multilevel generalized linear models to account for the potential intra-cluster correlation due to family unit and facility. In addition, we will adjust for potential confounding that may arise due to imbalances in children’s characteristics between study arms.

b) If the FAM-CARE program decline rate is substantial (>10%) and baseline characteristics of children differ significantly between those who accept FAM-CARE and those who decline, we propose to use the propensity score method to match and compare FAM-CARE and non- FAM-CARE participants. Using data from the FAM-CARE sites, we will estimate the probability of accepting FAM-CARE program given the baseline children and family characteristics. Using special matching algorithms, we will develop a statistical control group that will be compared with the FAM-CARE group. Regression modeling will be used to estimate the effect of the FAM-CARE group compared to the control group.

c) Finally, we will perform an intent-to-treat analysis in which all children at facilities offering the FAM-CARE program will be compared to all children at facilities without FAM-CARE program.

To answer primary aim 2, we will use the same statistical approach described for specific aim 1 above.

To answer secondary objectives 1 and 3, the analysis for the primary objective described above will be repeated using the appropriate outcomes.

To identify factors associated with viral suppression and HIV RNA >1,000 copies/mL (secondary objective 2), we propose to use multilevel logistic regression models to estimate the association between viral suppression and putative factors in each study arm. Examples of factors that might be evaluated include age and gender of child, when ART initiated and ART regimen, serious illness or hospitalization, timeliness of pharmacy drug pick-up, school attendance, family size, number of other HIV-positive individuals in family, HIV treatment and clinical status of other HIV-positive family members, disclosure of HIV status within family.

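### The arm comparison ignores the hospital versus health-center stratum used for allocation, and in the hospital stratum arm cannot be separated from hospital tier

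*Protocol*

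**What the plan says.** The regional description in the protocol (Description of HIV Services and EGPAF Program in Hhohho Region) sets out a tiered system that lists "national referral hospitals, regional hospitals, health centers, and primary health care facilities" as separate levels. It then counts the public facilities: "Of the 41 public facilities, 1 is a referral hospital, 1 is a regional hospital, 2 are health centers". A little further on, "the two hospitals and two health centers form 4 clusters of care facilities", and the hospital-headed clusters are those of Mbabane and Pigg's Peak.

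Figure 1 says that cluster selection was "stratified by whether health center vs hospital cluster". The Subject Population section gives the result: "The Emkhuzweni and Pigg’s Peak clusters were randomly selected to initiate FAM-CARE, while the Dvokolwako and Mbabane clusters will continue standard of care". Each stratum therefore has one cluster per arm.

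The Statistical Analysis Plan section describes a chi-square test of the two arm proportions, followed by a model: "We propose to use multilevel generalized linear models to account for the potential intra-cluster correlation due to family unit and facility". It adds adjustment for imbalances in children's characteristics, a propensity-score option built on acceptance of FAM-CARE within the FAM-CARE sites, and an intent-to-treat comparison of all children by type of facility. None of these uses the allocation stratum or compares the arms within a randomized pair.

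**The concern.** Stratifying the allocation and then pooling over the strata discards a design feature that was used. Here it also conceals something. By count, the two hospitals heading the clusters must be the one referral and the one regional hospital, and they sit in opposite arms. Whatever differs between these two levels of hospital, apart from FAM-CARE, enters the pooled estimate as part of the FAM-CARE effect. A reader given only a pooled difference cannot see how much of it comes from the pair in which the two hospitals differ in tier. The protocol says that a positive result would lead to wider roll-out, so how far the result can be attributed to FAM-CARE matters.

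**Working it through.** **Inputs.** Children aged 0-14 on ART at the study facilities (protocol Table 2):

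| Stratum | Control | FAM-CARE | Total |
|---|---|---|---|
| Health center | Dvokolwako 239 | Emkhuzweni 223 | 462 |
| Hospital | Mbabane 336 (hospital 248, clinic 88) | Pigg's Peak 398 (hospital 318, clinic 80) | 734 |
| All | 575 | 621 | 1,196 |

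**Planned effect, reproduced.** For 80% versus 90% suppression, two-sided 5%, 80% power:
n per arm = [1.96 x sqrt(2 x 0.85 x 0.15) + 0.842 x sqrt(0.8 x 0.2 + 0.9 x 0.1)]^2 / 0.10^2 = 199, or 398 in total. Then 199/0.9 = 222 per arm, or 444. This matches Table 3.

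**Share of children affected.**
- Hospital-cluster study sites: 734/1,196 = 61.4% (control 336/575 = 58.4%; FAM-CARE 398/621 = 64.1%).
- The two hospitals alone: (248 + 318)/1,196 = 566/1,196 = 47.3%.
- Over all clinics in Table 1, which is what the protocol calls its sampling frame: (488 + 587)/1,614 = 66.6%.

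**Shift in the pooled difference.** Assume a suppression difference t within the hospital stratum that has nothing to do with FAM-CARE, and enrollment in proportion to Table 2. Shift = t x share.

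| Assumed t (points) | Whole hospital cluster (x 0.614) | Hospitals only (x 0.473) |
|---|---|---|
| 2 | 1.2 | 0.9 |
| 5 | 3.1 | 2.4 |
| 10 | 6.1 | 4.7 |

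**Effect on the 5% test.** Take no FAM-CARE effect, 199 per arm, 80% suppression elsewhere, independent children and the whole-cluster shift. The simple two-proportion test rejects in about 12% of trials for t = 5, and in 31% to 37% for t = 10, depending on which hospital cluster does better.

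**What the planned methods can do.**
- A facility random effect can widen the standard error. With one hospital cluster per arm it cannot tell arm from tier.
- Adjustment for children's characteristics can reduce differences in measured case mix. It cannot reach unmeasured case mix or features of the hospital itself.
- A stratum term removes the leak caused by the arms having different hospital shares (64.1% - 58.4% = 5.7 percentage points). If the strata differed by 10 points in suppression, that leak would be about 0.6 points. The term respects the design but does not separate arm from tier.

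**Precision by pair.** Health-center share 462/1,196 = 38.6%; 0.386 x 398 = 154, or 77 per arm. Half-width = 1.96 x sqrt(0.8 x 0.2/77 + 0.9 x 0.1/77) = 0.11. For the hospital pair, 0.614 x 398 = 244, or 122 per arm, with half-width 1.96 x sqrt(0.25/122) = 0.09. Neither allows for clustering.

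**The case against.** Several counter-arguments have force, and they limit the point.

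- **Existing adjustment.** The plan already adjusts for imbalances in children's characteristics, and the schedule collects enrollment viral load, CD4 count and ART history in both arms. This stands: measured case mix is covered. Only residual and facility-level differences are left.
- **No evidence of a tier effect.** No suppression rates by tier are given, and the sentence on complex HIV cases groups hospitals with health centers rather than setting referral against regional. This stands: size and direction are unknown, and the figures above are assumptions. A reader might infer a tier effect from Table 2, where 2015 initiations relative to children on ART are 47/336 (14.0%) at the Mbabane sites and 25/398 (6.3%) at the Pigg's Peak sites. The table does not support this. At the hospitals the ratios are 22/248 (8.9%) and 22/318 (6.9%). Most of the gap comes from the two filter clinics, 25/88 and 3/80, which are of the same tier.
- **The clinics are not hospitals.** The 61% includes 168 children (88 + 80) at clinics. This stands, so the 47% is given beside it.
- **The allocation was random.** A coin toss is fair over repeated allocations. But one cluster per arm in a stratum cannot balance tier in the allocation that occurred.
- **A separate analysis plan may give results by pair.** It may. The protocol nevertheless has its own analysis section, which states the primary comparison, and that comparison leaves the stratum out.

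**Conclusion.** The point holds as a limit on attribution and as a mismatch between allocation and analysis. Arm and hospital tier coincide in the clusters that hold 61% of children on ART at the study facilities (47% at the hospitals themselves). The stated analysis neither uses the stratum nor shows the pairs separately. The shift of about 3 or 6 points rests on an assumed 5- or 10-point hospital-cluster difference and on enrollment following Table 2; the protocol sets no quotas by site.

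Two stronger readings should be resisted. A reader might take the health-center pair as a clean comparison. It lacks the tier difference, but it too has one cluster per arm, so any other cluster-level difference is equally mixed with FAM-CARE. A reader might also want to withhold a pooled effect unless the health-center pair points the same way. At about +/-11 points before clustering, the sign of that pair is too uncertain to carry such a rule. Nor do the documents show that a positive result would be spurious: they do not say which hospital is the referral one, and they give no outcome by tier.

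**What to change.** In the Statistical Analysis Plan section:

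1. Include the allocation stratum (hospital versus health center) in the primary model, or use a difference combined over the two strata, for both primary endpoints.
2. Beside it, report the month-18 FAM-CARE minus control difference with its interval for each randomized pair: Emkhuzweni versus Dvokolwako, and Pigg's Peak versus Mbabane.
3. State in the interpretation that the hospital-pair difference cannot be separated from hospital tier, and that each pair has only one cluster per arm.

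The cost is wording and one table; no new data are needed. The pair estimates will be imprecise (about +/-11 points for the health-center pair before clustering), and the claim becomes more guarded. These steps disclose the overlap of arm and tier. No analysis of these four clusters can remove it.
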